## AIM

### A. SPECIFIC AIMS

Our sample will consist of 370 families with a high school senior, half of whom will be assigned randomly to a prevention group (SAAF—EAP) and half of whom will be assigned to a control group. Pre-intervention, post-intervention, and follow-up assessments of youths' substance use and secondary outcomes will be conducted with the entire sample. Our specific aims are as follows:

1. To test the hypothesis that rural African American emerging adults randomly assigned to participate in SAAF—EAP, compared to control participants, will demonstrate lower rates of substance use initiation, and that those who already use substances (e.g., cigarettes; alcohol, including binge drinking; marijuana and other illicit substances) will use them less frequently and consume lower quantities, at each follow-up assessment.
2. To test the hypothesis that SAAF—EAP primary caregivers and emerging adults, compared to control participants, will report higher levels of autonomy-promoting parenting and responsiveness in family relationships at each follow-up assessment.

### D. RESEARCH METHODS

#### D1. Participants

A random sample of 370 rural African American families with a son or daughter in the last semester of public high school from each of 6 counties in central Georgia will participate in the study.

*D1.1. Random Assignment, Other Programs, and Contamination:* Families will be assigned randomly to either the prevention or control condition.

*D1.2. Inclusion/Exclusion criteria:* We will recruit all youth from public schools in their senior year of high school in the target counties that self-report being African American or Black and age 17-19. We will exclude from the pool of potential participants a small number of students whose participation in the intervention's group-based activities may create negative iatrogenic effects (Dishion, McCord, & Poulin, 1999). Students who have been suspended from school more than once and those who were expelled from a high school other than the one they are attending will be disqualified.

*D1.3. Family Recruitment and Retention Strategies:* The recruitment process will be carried out in the following sequence: (1) a letter will be mailed to parents/guardians from the school principal informing them of the study, (2) a home visit will be made by a community liaison to obtain active consent from primary caregiver and student to implement the screening procedures described previously, and (3) families will be invited to participate with active consent obtained from primary caregivers and active assent from emerging adults.

*D1.3a. Principals' letter:* Each primary caregiver of an African American high school senior who is selected randomly from the pool of potential participants will receive a letter from the school principal describing the study and the collaboration with the University of Georgia (UGA). Caregivers will be informed that they will be contacted by representatives associated with UGA (community liaisons) and they and their high school seniors may be invited to participate.

*D1.3b. Community liaisons' home visits:* Community liaisons will schedule initial home visits to families of students selected randomly from the potential participant pool. During this visit, the liaison will provide the family and student with information about the study and tell them that, based on school information, it is possible that they may be invited to participate. The community liaison will give consent/assent forms to the primary caregiver and student. A student will be classified as refusing at this point if (a) the caregiver or student does not wish to take part in the study or (b) the caregiver or student does not consent to allow UGA researchers to obtain school information. These students will be removed from the sample pool and will not be screened for the exclusionary criteria.

*D1.3c. Monetary incentives:* At each pretest, posttest, and follow-up assessment in the proposed project, emerging adults will receive \$50 and participating caregivers will receive \$100.

*D1.3d. Retention:* Following each home visit and prevention session, community liaisons contact participants to inquire about the quality of the experience and to answer questions. Between data collections, community liaisons call families on a regular basis. Community liaisons will obtain contact information for emerging adults who leave their parents' homes and call these young people directly at their own residences. In the event that a phone line is temporarily disconnected, community liaisons visit the families' homes or the residences of emerging adults who live apart from their families. The families also provide us with contact information for three individuals who will always know their whereabouts; these lists are updated at each home

visit. All emerging adults and their families will receive a semiannual newsletter that will include a stamped address correction form to facilitate the updating of address lists before post office forwarding orders expire.

**D2. Overview of the Prevention and Research Procedures**

All prevention and control families will participate in a pretest, a posttest, and a follow-up assessment that takes place 9 months after the posttest. Prevention families will participate in a 6-week intervention while control families receive, via postal mail, information about emerging adult development, stress, diet, and exercise. The posttest data collection will take place 3 months after prevention training concludes to allow any transitory immediate effects to dissipate. Table 3 presents the time line for all activities included in the scope of management, this proposal. If we are able to obtain additional funding later, we will continue to conduct booster sessions and follow-up studies with the families as the youths progress through emerging adulthood.

**Table 3. Time line.**

[figure not shown]

### D3. Prevention Development Plan

**D3.1. Development of the Prevention Program with the Assistance of Community Members:** Project staff will meet with two groups of 10 adults and two groups of 10 youths who are representative of the African American communities in the participating counties to discuss the prevention curriculum modules and the proposed training process. The focus group members will be asked for feedback about the propriety of the curriculum for rural African American families and emerging adults; the curriculum will be revised accordingly. The focus group will evaluate the revised curriculum to insure that the changes effectively addressed their suggestions.

A pilot intervention feasibility study will be conducted with a sample of 10 African American emerging adults and their parents. The pilot will be videotaped and a staff member from the Center will view the tapes and take notes on each session. Session logistics, as well as the relevance and appropriateness of activities and materials, will be assessed and any necessary revisions will be made to the final curriculum.

**D3.2. Implementation of the Prevention Program:** Procedures for recruiting and training the group leaders, insuring fidelity to the prevention curriculum, and engaging participating families will follow the same guidelines that [name] and [name] used successfully in SAAF ([name] et al, in press; [name] & [name], in press).

**D3.2a. Group leaders:** Three-person teams will lead prevention groups, each of which will include ~10 families. All group leaders will be African Americans. The leaders will receive 30 hours of training at the Center for Family Research of the University of Georgia. The training will address content delivery within a structured group process format, implementation of specific curriculum activities, guided practice in delivering and pacing curriculum segments, and leader self-care. Drs. [name], [name], [name], Brown, and [name], along with Prevention Coordinator [name], will prepare a leaders' guide. Didactic material, role-playing exercises, and modeling will be used to teach the protocol for each session. Prior to completion of training, group leaders must demonstrate mastery of the prevention programming by scoring 100% on a written examination covering

the prevention material. Leaders will meet with [name] for 2 hours each week to review the previous week's sessions and prepare for those in the coming week.

*D3.2b. Treatment integrity:* Standardized procedures will be followed to insure the prevention sessions' integrity. The intervention manual will include a detailed format to be used for each session. Each team will be provided with materials designed to facilitate correct execution of the session protocol, including an outline of each session, a checklist of the materials necessary for each activity, the specific theme of each task, and forms for in-session notes. Each session's content and instruction process will be documented on videotape. Leaders will receive ongoing supervision throughout the study, including unannounced direct observations by the field supervisor. To assess fidelity to the prevention program, videotapes of all sessions will be scored for coverage of the curriculum and adherence to the protocol. As in SAAF, fidelity instruments will be developed to score the caregiver, emerging adult, and family sessions. These strategies have been found to increase consistency among group leaders (Nye et al., 1995). Presentation of targeted processes on videotapes also will help to ensure the intervention's integrity.

*D3.2c. Logistics:* In each of the prevention counties, two meeting sites will be established at community facilities in central locations that are easily accessible to program participants. Local churches and schools provide ample space for classrooms, waiting areas, and parking.

*D3.2d. Engagement procedures:* Several strategies used in SAAF to address scheduling conflicts, transportation needs, and childcare requirements will be used in the proposed program. During the pretest data collection, family members will be asked about their weekly schedules and sessions will be planned to accommodate as many families as possible. During the first half hour of each meeting, dinner will be served to family members attending the prevention sessions. Leaders will arrange transportation for any families who need it and child care will be provided for any children who come with the families. An intensive reminder protocol also will be used throughout the course of the program. Community liaisons will call all participants before the program begins and prior to each weekly prevention session to encourage their involvement. Reminder postcards will be sent from the Center each week, highlighting the focus of the upcoming meeting. A community liaison will call any participants who miss a meeting to remind them of the next meeting and address any barriers to attendance.

*D3.3. Program Structure:* The delivery system used in the SAAF program will be adapted and used to structure the proposed intervention. The prevention program will consist of 6 consecutive weekly meetings, with separate family member and emerging adult skill-building curricula and a family curriculum. Each meeting will include separate, concurrent sessions for family members and emerging adults, followed by joint sessions during which the emerging adults and their family members review, discuss, and practice the skills they learned in their separate sessions. Videotapes portraying family interactions and intrapersonal processes will be used in the emerging adult, family member, and joint family sessions to ensure consistent presentation of key points. Each session will include a homework review, didactic presentation of information, group discussion, and skill-building activities that reinforce learning. The concurrent and family sessions will each last 1 hour; thus, emerging adults and family members will receive 12 hours of prevention training. During the same weeks that the intervention families participate in the prevention sessions, families in the control group will receive weekly leaflets via postal mail. They will describe emerging adult social, emotional, and identity development; stress management; and information about diet and exercise needs.

*D3.4. Prevention Program:* The content of the program is based on the causative model that we developed based on [name]'s and on [name] and [name]'s research programs. The prevention curriculum objectives for each session can be found in Appendix 6.

*D3.4a. Autonomy-promoting and responsive family relationships:* The caregivers' curriculum will focus on providing emerging adults with developmentally appropriate instrumental and emotional support; providing clear expectations for emerging adults' behavior; engaging emerging adults in discussions about future plans for meeting expectations and responsibilities; fostering racial pride; conveying adaptive strategies for coping with discrimination; modeling and encouraging nonavoidant ways of coping with various life stresses; developing strategies for maintaining affectively close and involved relationships while promoting autonomy; and articulating negative expectations for substance use.

*D3.4b. Self-control, future orientation, and emotion control:* The prevention topics for emerging adults will address setting goals and developing courses of action to meet them; using time productively and keeping commitments; identifying coping strategies to use when confronting financial, family, friendship, or

discrimination-related stress; applying nonavoidant, problem-focused coping strategies to various stressful situations; forming educational and occupational goals with step-by-step plans for attaining them; and dealing with institutional racism.

*D3.4c. Substance use prototypes and images:* The prevention topics for emerging adults include distinguishing unintentional from intentional behavior; understanding the prototypes or images that they hold of substance-using agemates; learning that most of their peers hold more negative than positive images of substance-using agemates; recognizing risk-conducive situations, forming plans to avoid risks; and considering actions they can take if they find themselves in high-risk situations.

#### D4. Data Collection

One 2-hour home visit will be made to each family for data collection at the pretest, posttest, and follow-up assessments that take place 9 months after the posttest. To minimize cultural bias, African American students and community members will serve as home visitors.

*D4.1. Intervention Assessment:* All self-report data from emerging adults and their parents will be gathered during private interviews with a researcher, with no other family members present or able to overhear the conversation. At no time during the presentation of the self-report instruments will the researchers assume that a family member can read; this literacy concern is one of the reasons for presenting the questionnaires in an interview format. The interviews will be conducted using Computer Assisted Interviewing (CAI) technology with laptop computers. One item at a time will be displayed on the computer screen; the interviewer will read each item to the participant and enter the answer into the computer. The use of CAI creates an easy interview pace; reduces missing data due to skipped questions, out-of-range responses and inconsistent answers; and increases administration consistency.

*D4.2. Process Evaluation of the Prevention Program:* We will use the number of program sessions attended to measure intervention exposure. Using session attendance and program fidelity data (see Section 3.2b), a dosage score will be calculated for each study participant. Both parents in two-parent families will be encouraged to attend each session of the program; in single-parent families, the parent and an extended family member who assisted with the emerging adult's upbringing will be encouraged to attend. If two adults cannot come, attendance of one will be encouraged as preferable to attendance of neither. At the end of each prevention session, the leaders will rate group responsiveness, engagement, and supportiveness using 5-point process evaluation scales.

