##### **D.6.1. Intervention Assessment**

Computer-assisted self-administered interviews using audio enhancements (ACASI) will be used to collect data from youth and caregivers. The interview measures will be administered via ACASI with the guidance of Assessment Assistants. The assistants, who will be blind to families' assignment to the SAAF–HS or attention-control condition, will arrange home visits with participants. The assistants will set up a computer for each family member at places in the residence that the family designates as private, then enter the participants' ID numbers and the commands necessary to begin the appropriate instruments. After leading the participants through a series of warm-up exercises and verifying that they are comfortable using the computers, the Assessment Assistants will remain available to help participants upon request. When data are returned to the CFR, the project coordinator will immediately check their completeness and integrity and ensure the ID numbers' accuracy. Within 8 business hours of data collection, a computer specialist will upload the data to a secure server; all data are backed up to a storage area network on an hourly basis.

**D.6.1a. Training of Assessment Assistants.** Assessment Assistants will be selected based on their previous experience with collecting data and interviewing adolescents about sensitive topics. Prior to administering the baseline assessment, they will receive 20 hours of intensive training and supervised practice that will address building rapport, using the ACASI system, and helping participants to use the system. Assistants also will meet each week with the Project Director to discuss any problems that arise. Prior to the follow-up assessments, training updates will be conducted in which any changes to the interview items or assessment procedures will be reviewed.

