**D.7.7b. High-risk sexual behavior.** The primary outcome for this variable is the proportion of vaginal and anal sexual acts in which condoms were used during the 30 days prior to the ACASI assessment. This measure is derived by dividing the number of protected encounters by the total number of encounters. This ratio is one of the most commonly used measures of outcome efficacy in HIV prevention trials (Celentano et al., 2002; Chesney et al., 2003; Gordon, Forsyth, Stall, & Cheever, 2005; Hobfoll et al., 2002; Rosser et al., 2002). Other self-reported sexual behaviors to be assessed include the number of unprotected vaginal and anal sexual encounters during the previous 3 months and condom use during the most recent instance of sexual intercourse. Information on number and types (primary, casual, new) of sexual partners; frequency of oral, anal, and vaginal sex; use of alcohol and other drugs prior to sexual intercourse; STD infection; pregnancy; and partners' risk status (e.g., sexual partner has other partners) will also be gathered.

Researchers widely recognize that participants' reports of their sexual practices might be inaccurate, either unintentionally or intentionally. We will take several steps to increase the self-report measures' validity. To minimize inaccurate recall, only sexual behavior that occurred during a relatively brief time period (i.e. during the past 30 days, during the past 3 months, and at last sexual intercourse) will be addressed. Participants also will be given a calendar on which the relevant dates are clearly marked. ACASI methodology also has been demonstrated to increase respondents' willingness to provide frank responses to sensitive questions about their sexual behavior (Macalino et al., 2002).

**D.7.7c. Deviant behavior.** Theoretically, antisocial behavior is related to substance use and high-risk sexual activity (Jessor, 1991), perhaps through a common cause such as parents' ineffective monitoring and discipline (Leigh & Stall, 1993). Adolescents will use a checklist from the National Youth Survey (Elliott, Ageton, & Huizinga, 1985) to report their own deviant behavior during the past 3 months and the proportion of their friends who engaged in the same behavior during that time period.

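### AIM takes its Aim 1 substance-use answers aloud by interviewer, with no masking described, and only one arm attends sessions with substance-use content; arm-dependent under-reporting is possible and cheap to reduce

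*Combined protocol and SAP*

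**What the plan says.** **Mode.** AIM D4.1 covers every self-report measure: "All self-report data from emerging adults and their parents will be gathered during private interviews with a researcher". The interview is computer-assisted, but "the interviewer will read each item to the participant and enter the answer into the computer". The privacy offered is from the household, "with no other family members present or able to overhear the conversation"; the interviewer hears every answer.

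**Who asks.** AIM D4 says that "African American students and community members will serve as home visitors". Neither D4 nor D4.1 says whether these visitors know the family's assignment.

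**Outcome.** AIM's Specific Aims set substance use apart from the rest: "follow-up assessments of youths' substance use and secondary outcomes will be conducted with the entire sample". Aim 1 is about substance use, so it is primary in effect, although the text does not use that word. D5.8 and D6.2 define it wholly from participants' reports.

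**Contact by arm.** Prevention families have six weekly meetings (D2, D3.3), while "control families receive, via postal mail, information" on development, stress, diet and exercise. Among broader topics, the youth curriculum covers images of substance users and ways to avoid risky situations (D3.4c). The caregiver curriculum includes voicing negative expectations about use (D3.4a). Posttest comes three months after training ends, and follow-up nine months after that (D2).

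**Companion trial.** SAAF-T D.6.1 uses audio computer-assisted self-interview for youths and caregivers. Of its assessment staff it says "The assistants, who will be blind to" assignment.

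**The concern.** A youth who has attended sessions touching on substance use, some of them jointly with a caregiver, may feel more pressure than a control youth to give the approved answer when it must be spoken to a study representative. If so, observed use falls further below true use in the prevention arm than in the control arm, and the difference looks like benefit. A visitor who knows the assignment could add to this through tone, probing or coding.

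Under-reporting that is equal in both arms would not raise the false-positive rate; the arm-dependent part is what matters. None of the planned methods addresses it. Full-information maximum likelihood and multiple imputation (D6.1b) deal with answers that are absent, not answers that are wrong. The intent-to-treat rule (D6.1c) keeps the groups as randomised but takes reports at face value. The growth, Tobit and zero-inflated models (D6.4a) also treat the reported value as the outcome. With no objective measure, the data could not later separate less use from less disclosure. At stake is the interpretation of AIM's leading hypothesis.

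**Working it through.** **1. The two protocols side by side**

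| Feature | AIM | SAAF-T |
|---|---|---|
| Who enters the answer | Interviewer, after hearing it (D4.1) | Participant, by audio self-interview (D.6.1) |
| Masking of assessment staff | Not described | Stated (D.6.1) |
| Control condition | Mailed leaflets (D2, D3.3) | Programme of identical structure (D.5) |

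SAAF-T has three features that limit arm-dependent reporting. AIM describes none of them.

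**2. Illustration of what differential disclosure would do**

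The plan gives no figure to reproduce here. Inputs:

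- Sample: 370 families, half per arm (AIM Specific Aims), less the 15% attrition in D6.3: 370 × 0.85 / 2 = 157 per arm. D6.3 itself speaks of 690 families; 370 is used because the Specific Aims and D1 both state it.
- True use: 40% in both arms, so no real effect. Assumed; AIM gives no rate.
- Share of users who disclose: 90% in controls; 85% or 80% in prevention. Assumed.
- Test: unadjusted two-proportion z test, two-sided .05.

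Observed rate = true rate × disclosure share: control 0.40 × 0.90 = 0.36; prevention 0.40 × 0.85 = 0.34, or 0.40 × 0.80 = 0.32.

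Odds ratio, control against prevention: (0.36/0.64)/(0.34/0.66) = 1.09, or (0.36/0.64)/(0.32/0.68) = 1.20.

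With d the observed difference, p̄ the mean of the two rates and n = 157, SE0 = √(2p̄(1−p̄)/n) and SE1 = √([p1(1−p1)+p2(1−p2)]/n). Rejection probability = Φ((d − 1.96·SE0)/SE1) + Φ((−d − 1.96·SE0)/SE1).

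- 36% against 34%: SE0 = 0.0538, critical difference 0.1055, SE1 = 0.0538. Φ(−1.59) + Φ(−2.33) = 5.6% + 1.0% = **6.6%**.
- 36% against 32%: SE0 = 0.0535, critical difference 0.1048, SE1 = 0.0534. Φ(−1.21) + Φ(−2.71) = 11.3% + 0.3% = **11.6%**.
- Equal disclosure, 36% against 36%: 5.0%.

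The first term in each sum is a false finding of benefit, nominally 2.5%.

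**3. Range over the assumptions** (two-sided rejection, same test and n)

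| Disclosure, control / prevention | 30% true use | 40% | 50% |
|---|---|---|---|
| 90% / 90% | 5.0% | 5.0% | 5.0% |
| 90% / 80% | 9.3% | 11.6% | 14.6% |
| 100% / 90% | 9.0% | 11.3% | 14.4% |
| 100% / 80% | 22.3% | 31.4% | 42.9% |

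At the .01 level named in D6.3, the two cases in step 2 give 1.5% and 3.4% against a nominal 1%. If prevention youths were more candid than controls, the sign would reverse and a true benefit would be masked.

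**The case against.** The strongest reply is that this is the ordinary limitation of self-report, joined to a preference for another trial's method. Several parts of it stand.

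- *The visitors know the arm.* A reader might infer this, but AIM is silent. It describes group leaders and community liaisons separately from home visitors, and nothing says that visitors deliver the programme. The sound statement is that masking is not described.
- *Measurement comes straight after the sessions.* It does not. Posttest is three months later, expressly so that transitory effects can fade. That weakens the mechanism without excluding it.
- *Youths are drilled against substance use.* This overstates the programme. The negative-expectations topic belongs to the caregivers' curriculum, and the youth topics are mostly goals, coping and discrimination, with substance-use images and risk avoidance as one part.
- *Literacy is the only reason for reading aloud, and audio answers it.* AIM calls literacy one of the reasons. It also credits computer-assisted interviewing with easier pace, less missing and inconsistent data, and consistent administration. That audio would serve weak readers is an inference.
- *The documents show that audio self-interview makes substance-use reports franker.* SAAF-T D.7.7b says only that it increases willingness "to provide frank responses to sensitive questions about their sexual behavior". That is another topic, and it concerns candour overall rather than a difference between arms.
- *The illustration measures the bias.* It does not. Every disclosure rate is assumed, and so is the direction. AIM also plans event-history and growth models rather than this simple test.

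What does not stand is that only a clarification is needed. An answer spoken to a study representative, unequal exposure to substance-use content and no objective check together leave AIM's leading outcome open to a bias that the planned analyses cannot detect. A less exposed method is already in use in the companion trial.

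**Conclusion.** The concern holds as a design risk, not as a demonstrated bias. AIM's Aim 1 outcome is spoken to an interviewer whose masking is not described, and only the prevention arm attends sessions with substance-use content. More under-reporting in that arm would favour efficacy, and nothing in the analysis plan would reveal it. On the assumed figures (40% true use, 90% disclosure against 85% or 80%, 157 per arm, unadjusted two-sided .05 test), the false-positive rate would be 6.6% or 11.6%. Other assumptions give other values, and equal disclosure gives 5%. The documents supply neither the size nor the direction of any difference in disclosure, so these figures show sensitivity only. The change is worth making because it is small and protects the leading outcome; it is not a fatal flaw.

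**What to change.** 1. In AIM D4.1, state that home visitors are masked to assignment at posttest and follow-up.
2. Have participants hear and key the D5.8 substance-use items themselves, by audio self-interview on the laptops already planned. Other scales can stay interviewer-read.
3. Use the same mode at pretest, so that baseline and later waves are comparable.

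**Cost.** Masking needs wording and attention to how visits are assigned. Self-entry needs audio recording and programming for one section. That section may have more skipped or inconsistent answers, which AIM credits its computer-assisted interviewing with reducing.

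**What remains.** Masking cannot hide from participants whether they attended sessions, and self-entry lowers the pressure of disclosing aloud without abolishing it. Reports of AIM's substance-use results should still name arm-dependent self-report as a limitation.
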